### Blinding

#### Masking

In this trial, both outcome assessors and data analysts will be blinded after intervention assignment. They will not know the participants’ intervention group affiliations during outcome assessment or data analysis. Due to the intervention’s nature, involving educational sessions and exercises requiring interaction, participants and educators cannot be blinded.

#### Emergency unmasking

A secure process, such as a password-protected system, will be employed for the emergency unmasking. Unbinding should only occur when deemed necessary, with the objective of preserving the trial’s integrity.

#### Data collection plan

The trial will collect baseline and outcome data through questionnaires, laboratory tests, and physical assessments, using standardized and validated instruments to ensure data quality. The instruments used in the trial are validated, and information on them can be found in the protocol.

#### Data collection plan: Retention

To ensure that participants remain engaged and complete the follow-up procedure in our trial, several strategies have been implemented. Firstly, clear and concise information is provided to participants, explaining the trial’s details, potential benefits, and associated risks, to help them understand the importance of their participation. Secondly, clear communication channels were established between the research team and participants to encourage an open and trusting relationship. The environment encourages participants to ask questions and provide feedback comfortably. Additionally, regular follow-up phone calls or emails are conducted to remind participants of upcoming study visits and to address any concerns they may have.

#### Data management

All data will be entered into a secure database system with restricted access. Data quality will be maintained through the implementation of range checks and double data entry processes. Tight data security and storage plans are in place, including regular backups, restricted access, and secure transfer methods.

#### Statistics: Outcome

Data analysis will be conducted using the statistical software SPSS version 25.0 (SPSS Inc., Chicago, IL, USA). A descriptive analysis of the demographic characteristics and pain intensity of the sample size will be performed, presenting continuous variables as mean ± standard deviation (SD) and 95% confidence interval (CI), while categorical variables will be presented as number (n) and percentage (relative frequency, %). In instances where quantitative variables follow a non-normal distribution, they will be described using the median and interquartile range.

For the comparison between groups, parametric tests based on the central limit theorem will be chosen, since the sample size of both groups will be greater than 30 [56]. A mixed-model Analysis of Covariance (ANCOVA) will be used including baseline as the covariate, to obtain between-group adjusted mean differences at each follow-up point, controlling for type I error rate using Bonferroni’s correction. The chi-square test will be used for nominal variables. If the criteria for parametric testing cannot be met, robust methods will be applied [57]. A p-value < 0.05 will be accepted as statistically significant.

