**Methods:**

In this single-blind, randomized clinical trial, patients will be randomly assigned to one of two groups: one will receive exercise with TE and the other without TE. Assessments will be made at baseline, mid-treatment, post-intervention, and at one and eight months.

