## Outcomes

### Primary outcome

#### Pain intensity

*Visual Analogue Scale (VAS)*. Pain intensity will be measured using a 100 mm visual analog scale where 0 represents ‘no pain’ and 100 the ‘worst pain imaginable’. Participants draw a mark at a point on the line that best reflects the pain they are experiencing at the time of measurement. Higher scores indicate higher pain levels. The sensitivity and specificity of this questionnaire and the acceptability of its psychometric properties have been approved [42].

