#### Sample size

The determination of the sample size used a t-test for independent means, calculated using G*Power software (Universität Düsseldorf, Germany). The significance level was set at 0.05, and a power of 90% was targeted. The effect size, assessed by Cohen’s d, was predicted based on a mean difference of 2 points in the Visual Analog Scale (VAS), as it is commonly considered the minimum clinically relevant change in many chronic pain conditions [55], and the pooled standard deviation (SD_pooled). This was derived from the standard deviations of the intervention and control groups in a preliminary study, which were 1.29 and 2.61, respectively.

In recognition of the potential underestimation of standard deviations in the pilot study, the original SD values were adjusted using the Upper Confidence Limit (UCL) method, as described by Whitehead et al. [56], based on Browne’s [57] approach. This adjustment, accounting for a 95% confidence level, yielded an SD of 3.227 using the formula [56, 57]: s_UCL^2 = [k/(X_(1-X,k)^2)] s^2.

Consequently, the effect size (d) was calculated as 0.619195 (derived from 2/3.23). With a 1:1 allocation ratio between groups, G*Power [58] indicated a requisite minimum of 56 subjects per group to detect a 2-point difference in VAS with 90% power. Considering a 15% dropout rate, the final sample size was set at 66 subjects per group, totaling 132 subjects for the study to maintain the desired statistical power.

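### The 90% power was worked out for one t-test of VAS at 0.05, but the protocol names no primary visit and plans Bonferroni-corrected comparisons at every follow-up, so the 90% is not established for the planned analysis

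*Protocol article*

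**What the plan says.** The Primary outcome section (Pain intensity) defines the measure, "Pain intensity will be measured using a 100 mm visual analog scale", and gives no visit at which it is primary. The abstract lists the visits: "Assessments will be made at baseline, mid-treatment, post-intervention, and at one and eight months". The Outcomes section repeats this schedule for all outcome measures. There are therefore four post-baseline visits.

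Under Statistics: Outcome, a mixed-model ANCOVA with baseline as covariate is to be used "to obtain between-group adjusted mean differences at each follow-up point, controlling for type I error rate using" Bonferroni's correction. No visit is singled out. The number of comparisons in the Bonferroni family is not given, and neither is the pattern of results that would count as success on the primary outcome.

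Under Sample size: "The determination of the sample size used a t-test for independent means". "The significance level was set at 0.05, and a power of 90% was targeted". The section arrives at 56 per group, raised to 66 for 15% dropout. It does not mention several visits, a corrected significance level or a baseline covariate.

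**The concern.** The sample size section and the analysis section describe different decision rules. One has a single comparison at 0.05. The other has a comparison at each follow-up visit under a Bonferroni threshold, which for four visits is 0.05/4 = 0.0125. A stricter threshold with the same number of patients lowers the power of each comparison, and nothing in the protocol shows that something else makes up the loss.

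The missing primary visit matters for interpretation as well. A group difference only at mid-treatment, before the programme has ended, and a difference only at eight months are different claims about the intervention. As written, either could be presented as the primary result. The 2-point difference used for sizing is not tied to any visit either.

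**Working it through.** **Inputs, all from the Sample size section.** The difference is "a mean difference of 2 points in the Visual Analog Scale (VAS"), evidently in 0–10 units; d has no unit, so this does not affect power. For the SD, the pilot adjustment "yielded an SD of 3.227 using the formula" cited there. Then "the effect size (d) was calculated as 0.619195 (derived from 2/3.23"). Allocation is 1:1, with 56 evaluable per group and 15% dropout. Sidedness is not stated.

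**Formula.** Two-sample t-test with n per group: df = 2n − 2, noncentrality = d·√(n/2), and power from the noncentral t distribution at the two-sided critical value.

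**Step 1: reproduce the stated figure.** d = 2/3.23 = 0.6192. With n = 56, df = 110 and noncentrality = 0.6192 × √28 = 3.276. At two-sided 0.05 the critical value is 1.982 and power is 90.1%. The smallest n reaching 90% is 56, and 56/0.85 = 65.9, so 66. A one-sided test would need only 46, so the calculation was two-sided. The stated sample size is correct for the test it names.

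**Step 2: apply the Bonferroni threshold, same d and n = 56, no covariate.**

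| Visits in family | Alpha per visit | Power at one visit |
|---|---|---|
| 1 | 0.05 | 90.1% |
| 2 | 0.025 | 84.1% |
| 3 | 0.0167 | 79.9% |
| 4 | 0.0125 | 76.8% |

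With all 66 per group retained and a family of four, power is 84.5%. To reach 90% per visit at 0.0125 on this basis takes 77 evaluable per group, or 77/0.85 = 90.6, so 91 randomised.

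**Step 3: allow for the planned baseline adjustment.** If the SD used is that of follow-up VAS, and r is the within-group correlation of baseline with follow-up VAS, the effective effect size is d/√(1 − r²). The protocol gives no r, so these values are assumptions (n = 56, alpha 0.0125):

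| Assumed r | Effective d | Power at one visit |
|---|---|---|
| 0.3 | 0.649 | 81.3% |
| 0.5 | 0.715 | 89.1% |
| 0.52 | 0.725 | 90.0% |
| 0.6 | 0.774 | 93.8% |

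**Step 4: allow for the unstated success rule.** I simulated four visits with the 2-point effect at each, no covariate, n = 56 and alpha 0.0125 per visit, at assumed between-visit correlations of 0.5, 0.7 and 0.9. Significance at one visit or more has power of about 96%, 92% and 86%. Significance at all four has power of about 50%, 57% and 66%.

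**The case against.** The strongest reply is that 77% is not the power of the planned analysis. It joins the Bonferroni threshold of the analysis section to the unadjusted t-test of the sample size section, whereas the plan is a baseline-adjusted ANCOVA. It also assumes a family of four, which the protocol does not state, and the full 15% loss at the visit in question. This stands. A reader might infer that the trial simply has 77% power, or that it must recruit 91 per group. The documents support neither. The figure of 77% is per-visit power with no gain from the covariate, and a baseline correlation of about 0.52 or more would restore 90%.

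Nor can one say that power falls short under the planned rule, because no rule is stated. If significance at any one visit suffices and the effect holds at all four, power is about 86% to 96%.

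The sizing also carries a deliberate margin. The SD of 3.227 is an upper confidence limit, and the larger of the two pilot SDs was 2.61. At 2.61, 56 per group at 0.0125 would give about 93%. This makes a real shortfall less likely, but the 90% claim is made at the inflated SD, so it must be judged there.

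Finally, a reader might infer that the missing primary visit leaves false positives uncontrolled. It does not: Bonferroni applied across all the VAS visits controls the type I error among them. What it cannot do is say which visit answers the primary question.

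None of this removes the mismatch. The sample size section uses neither a covariate nor a corrected alpha, so the protocol offers no basis for 90% under its own analysis.

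**Conclusion.** The point holds as a mismatch between two sections, and the power statement is wrong as written. The 56/66 per group gives 90% for one t-test at two-sided 0.05, and that is not the comparison the analysis section plans.

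On the protocol's unadjusted basis with 56 per group, per-visit power is about 77% for a family of four, 80% for three and 84% for two. With baseline adjustment and a family of four it is about 81% to 94% for assumed correlations of 0.3 to 0.6. Depending on whether one visit or all four must be significant, overall power on the unadjusted basis could be anywhere from about half to 96%. The correlations, the family size and the success rule are my assumptions. The difference, SD, sample size and alpha are the protocol's. What is shown is that 90% is unsupported, not that the trial is necessarily underpowered.

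**What to change.** Before unblinded data are seen, name VAS at one visit (for example the end of the 4-week programme) as the single primary comparison, tested at two-sided 0.05. Make the other three visits secondary, with Bonferroni or Holm among them. State in the Sample size section that the 2-point difference refers to the chosen visit and that the test is two-sided. Then 56/66 per group and 90% agree as they stand, and baseline adjustment is a bonus.

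If the sponsor prefers to keep all four visits primary, state the Bonferroni family and the success rule (any visit or all visits). Then either restate per-visit power as about 77% unadjusted, or give and justify the baseline correlation that supports a higher figure.

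The first option costs a few sentences in the outcome, sample size and statistics sections, and no patients. Its small downside is that three visits lose primary status.

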#### Others

*Pressure Pain Thresholds (PPT)*. Pressure pain thresholds will be assessed through a pressure algometer. The algometer will be applied to different points in the body (elbow and knee) and participants will be asked to indicate the point at which pressure changes to pain. The pressure will be gradually increased at approximately 1 kg/s until the participant indicates feeling pain. The threshold pressure at which the sensation changes from pressure to pain will be recorded in kilograms (kg) and used as an indicator of PPT. Higher PPT values indicate higher pain thresholds. The validity and reliability of using a pressure algometer to measure PPT have been established [53].

*Height and weight*. Both these variables will be determined by patient estimation, with no exploration of them in the measurement process.

*Sociodemographic*. This comprises Age, Marital status (Single, Married, Divorced, Widowed), Employment status (Active, Unemployed, Retired, Temporary disability, Student, Homemaker, Other), Educational level (none, primary, secondary, university), and Gender.

*Exercise*. Among the exercise variables, the parameters described below will be considered:

*Blood pressure and respiratory rate*. Measured with the Anura application, which has demonstrated reliability with a conventional blood pressure measurement of 98% [54].

*Saturation and HR* are Measured with an Oxylink finger pulse oximeter.

All the outcome measurements will be assessed in a random order at baseline, at the halfway point of the treatment, post-intervention, and one- and eight-months post-intervention (Figs 3–5).

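### Bonferroni across the follow-up visits is valid, but Holm's step-down procedure gives the same family-wise error control and never rejects less: a cheap improvement, not an error

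*Protocol article*

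**What the plan says.** The section Statistics: Outcome plans a mixed-model ANCOVA with the baseline value as covariate "to obtain between-group adjusted mean differences at each follow-up point, controlling for type I error rate using" Bonferroni's correction. The same section adds "A p-value < 0.05 will be accepted as statistically significant". It does not say how many comparisons form the family, or whether the correction runs within each outcome.

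Under Secondary outcomes, Others, the outcomes are scheduled "at baseline, at the halfway point of the treatment, post-intervention, and one- and eight-months post-intervention". That makes four post-baseline assessments. Whether the mid-treatment one counts as a follow-up point is not said.

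The section Sample size is built on a single comparison: "The significance level was set at 0.05, and a power of 90% was targeted".

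**The concern.** The analysis is meant to show at which visits the arms differ. Plain Bonferroni holds every visit to the same strict threshold of 0.05/m, where m is the number of visits in the family. Holm applies that threshold only to the smallest p-value and then relaxes it step by step. With m = 4 the thresholds are 0.0125, 0.0167, 0.025 and 0.05. Holm's validity, like Bonferroni's, does not depend on the correlation between visits.

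If the education programme works at several visits, Bonferroni is more likely to leave some of them non-significant. A steady effect could then be read as fading or delayed.

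**Working it through.** **Inputs.** From Sample size: difference 2 VAS points, SD 3.227 (used as 3.23), d = 0.619195, 56 per arm before dropout, alpha 0.05, power 90%. From the visit schedule: four post-baseline assessments. Assumed because the article does not give them: family size m (4, with 3 and 2 as alternatives), equal between-visit correlation of 0.3 to 0.7, two-sided tests, and the number of visits with a true effect.

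**The plan's own figure.** d = 2/3.23 = 0.619. A two-sample t-test with noncentral t and two-sided alpha 0.05 needs 56 per arm (power 0.901). With 15% dropout, 56/0.85 = 65.9, so 66 per arm and 132 in total. The stated size reproduces.

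**Bonferroni power at one visit (normal approximation).** The mean of the z-statistic is d√(n/2) = 0.619195 × √28 = 3.276. Power is Φ(3.276 − z), where z is the two-sided critical value at 0.05/m.
- m = 4: z = 2.498, Φ(0.779) = 0.78
- m = 3: z = 2.394, Φ(0.882) = 0.81
- m = 2: z = 2.241, Φ(1.035) = 0.85

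**Holm by simulation.** 200,000 replicates of correlated z-statistics with 56 per arm. Average power over the visits that carry the effect, with the range for correlation 0.3 to 0.7:

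| Family | Visits with effect | Bonferroni | Holm |
|---|---|---|---|
| 4 | 4 | 0.78 | 0.85–0.87 |
| 4 | 3 | 0.78 | 0.82–0.83 |
| 4 | 2 | 0.78 | 0.80 |
| 4 | 1 | 0.78 | 0.78 |
| 3 | 3 | 0.81 | 0.87–0.88 |
| 2 | 2 | 0.85 | 0.88–0.89 |

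**Consistency across visits.** With four visits all affected, the chance that all four are significant is 0.47 to 0.59 with Bonferroni and 0.70 to 0.77 with Holm. The chance of a mixed result, with some visits significant and others not, is 0.52 to 0.34 with Bonferroni and 0.28 to 0.16 with Holm, as correlation goes from 0.3 to 0.7.

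**Error control.** With no effect anywhere and m = 4, the family-wise error is the same for both methods: 0.047, 0.043 and 0.037 at correlation 0.3, 0.5 and 0.7. With effects at some visits only, Holm uses more of the allowed error at the unaffected visits (for example 0.038 against 0.023 with two of four affected, correlation 0.5). It stayed below 0.05 in every pattern.

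**At least one significant visit.** This is identical for the two methods in every pattern (for example 0.96 for both with four affected visits and correlation 0.5), because Holm's first step is the Bonferroni threshold.

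**The case against.** The strongest case for leaving the plan alone has four parts.

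- **Bonferroni is not wrong.** It is valid under any dependence between visits, and the article does not contradict itself on it. This stands. A reader might infer a statistical error, and the text does not support that.
- **Bonferroni buys something.** The analysis is framed around adjusted mean differences, and Bonferroni supplies simple simultaneous intervals that agree with its tests. This stands too, so it would be too strong to say that power is given up for nothing. Its weight is limited because the article mentions 95% intervals only for descriptive summaries and promises no simultaneous intervals for these differences.
- **The largest gain is the best case.** It needs the full 2-point effect at every visit, including halfway through a four-week programme, and a family of four. The article states neither, so a threshold of 0.0125 per visit is an assumption. The planning SD is also deliberately inflated. With the pilot SDs of 1.29 and 2.61, pooled with equal weights, the SD is √((1.29² + 2.61²)/2) = 2.06, and both methods exceed 99% power per visit. This limits the size of the gain but does not reverse its direction.
- **Holm does not cure misreading.** With four real effects it still misses at least one in 23 to 30% of trials. The better guard is to read the adjusted mean differences themselves, which the plan already provides. Holm only makes a mixed result less frequent.

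**Conclusion.** This is an efficiency improvement to a valid plan. As a testing rule Holm is never worse than Bonferroni at the same family-wise level. At the planning effect the gain in average per-visit power is about 7 to 9 points if all of four visits are affected, 4 to 5 if three are, 2 if two are, and none if one is. For smaller families with every visit affected it is about 6 to 7 points (three visits) or 3 to 4 (two visits).

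These figures rest on the assumed family size and correlations and a common d = 0.619, and they leave out any precision gained from the baseline covariate. The article gives effect figures for VAS only. The ordering of the two methods carries over to BDNF, the questionnaires and pressure pain thresholds, but the size of the gain there is unknown.

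A reader might also infer that Holm would restore the targeted 90% power. It would not. The sample size uses alpha 0.05 for one comparison while the analysis splits alpha across visits. One visit tested at 0.0125 with 56 per arm has power 0.77 (noncentral t, no covariate), and Holm's first step uses that same threshold. That mismatch is a separate matter.

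**What to change.** In Statistics: Outcome, replace Bonferroni's correction with Holm's step-down procedure across the follow-up visits within each outcome. State how many visits form the family and whether mid-treatment is one of them. Report Holm-adjusted p-values beside the adjusted mean differences and their confidence intervals.

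The cost is a one-word change of method, a sentence on the family, and a few minutes of computation from the unadjusted p-values. No extra data or participants are needed. Because Holm has no simple matching simultaneous intervals, the plan should say whether the intervals shown are Bonferroni-adjusted or unadjusted, and note that they may occasionally disagree with the Holm test. The change should be made before any unblinded analysis.

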#### Statistics: Additional analyses

We will employ a multiple linear regression model to evaluate the strength of the associations between multiple predictor variables and the outcome variable at baseline. By using this method, we aim to discern the relative contribution of each predictor to the outcome, controlling for the potential influence of other variables, which will provide a comprehensive understanding of the factors that are most significantly associated with the baseline measures. We have calculated the sample size required to ensure a minimum power for each of the individual regression coefficients of the model. The sample size calculation was based on Hsieh et al. [59]. It was expected a minimum correlation coefficient of 0.6 between the predictors and the dependent variable, and an interpreter correlation of 0.5, along with a total of 8 predictors and a statistical significance level of 0.05, we determined that a minimum of 53 subjects is needed to achieve a desired power of 90% (beta of 0.1), assuming a loss rate of 15%. Thus, we ensured the feasibility of these tests with the previously reported sample size calculation for the main outcome.

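### The 53 subjects said to give 90% power for each of 8 regression coefficients give about 22% under the protocol's own correlations, and the full 132 give about 48%

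*Protocol article*

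**What the plan says.** Statistics: Additional analyses plans a multiple linear regression at baseline to separate the contribution of each predictor while controlling for the others. On its power the article says: "We have calculated the sample size required to ensure a minimum power for each of the individual regression coefficients of the model". The assumptions are "It was expected a minimum correlation coefficient of 0.6 between the predictors and the dependent variable, and an interpreter correlation of 0.5" (the odd word is read here as inter-predictor), "along with a total of 8 predictors and a statistical significance level of 0.05". The result is that 53 subjects suffice for 90% power, with a 15% loss rate allowed for. The paragraph ends by concluding that the sample size set for the main outcome makes these regression tests feasible. The Sample size section gives that number as 132, from 56 per group before dropout.

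**The concern.** A simple correlation and an adjusted regression coefficient are different quantities. When 8 predictors share much of their information, each one's contribution given the other 7 is far smaller than its correlation with the outcome. A variance inflation factor (VIF) corrects for the precision lost to correlated predictors. It does not shrink the effect itself. If 0.6 went into the calculation as the adjusted effect, the required number is far too small.

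The regression is meant to show which factors matter most at baseline. If readers believe each coefficient was tested with 90% power, they may take a non-significant coefficient as evidence that the predictor contributes nothing. At the true power such a result would be common even for predictors that do contribute.

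**Working it through.** **Inputs.** From Statistics: Additional analyses: predictor-outcome correlation 0.6, inter-predictor correlation 0.5, 8 predictors, alpha 0.05, power 90%, loss 15%. From Sample size: 132 enrolled, and 2 × 56 = 112 before the dropout allowance. Sidedness is not stated; two-sided is assumed because only that reproduces 53. The text of the cited method is not at hand, so the route below is inferred from the fact that it yields the protocol's number.

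**1. Reproducing 53.**
- Number for one correlation of 0.6 (Fisher z): [(1.960 + 1.282)/atanh(0.6)]² + 3 = 24.87.
- R² of one predictor on the other 7: 7 × 0.5²/(1 + 6 × 0.5) = 0.4375, so VIF = 1/(1 − 0.4375) = 1.778.
- 24.87 × 1.778 = 44.2, rounded up to 45.
- 45/0.85 = 52.9, rounded up to 53.

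Other routes miss it: a one-sided test gives 45, R² = 0.25 gives 40, R² = 0.5 gives 59, and no VIF gives 30. The common correlation of 0.5 among all 8 predictors is therefore the protocol's own structure.

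**2. The adjusted effect those correlations imply.**
- Standardised coefficient: 0.6/(1 + 7 × 0.5) = 0.6/4.5 = 0.133.
- Model R²: 8 × 0.6 × 0.133 = 0.64.
- f² for one coefficient: 0.133² × 0.5625/(1 − 0.64) = 0.0278.
- Partial correlation: √(0.0278/1.0278) = 0.164.

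**3. Power per coefficient** (two-sided noncentral t, n − 9 degrees of freedom, noncentrality √(n × f²)):

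| Analysed | Power |
|---|---|
| 45 (53 less 15%) | 19% |
| 53 | 22% |
| 112 | 42% |
| 132 | 48% |
| 381 | 90% |

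Simulation with random predictors gives slightly less: 17% at 45, 19% at 53, 45% at 132.

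**4. Other readings of 0.6.**
- As a standardised coefficient for all 8: the explained variance would be 0.6² × (8 + 56 × 0.5) = 12.96 on an outcome scaled to variance 1, which is impossible.
- As a partial correlation for all 8: f² = 0.36/0.64 = 0.5625, so β² = 1 − R². With R² = 36β², R² = 36/37 = 0.97. This is possible but implausible, and each simple correlation would then be 4.5 × 0.164 = 0.74, not 0.6.

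**5. Sensitivity of power to the two planning correlations.**

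| Predictor-outcome | Inter-predictor | Model R² | n = 53 | n = 132 |
|---|---|---|---|---|
| 0.60 | 0.4 | 0.76 | 46% | 85% |
| 0.60 | 0.5 | 0.64 | 22% | 48% |
| 0.60 | 0.6 | 0.55 | 13% | 26% |
| 0.65 | 0.5 | 0.75 | 34% | 70% |
| 0.70 | 0.5 | 0.87 | 64% | 96% |
| 0.72 | 0.5 | 0.92 | 86% | above 99% |

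If one predictor sits at 0.6 and the other seven at 0.65 (inter-predictor 0.5), its coefficient falls to 0.056 and its power at 132 is about 15%.

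**6. What 132 does deliver.** With 8 predictors and two-sided alpha 0.05, 90% power is reached at a partial correlation of about 0.27 to 0.28.

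**The case against.** The case for the protocol has several parts.

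- **The arithmetic is sound.** This is true: 53 follows from the VIF formula. The fault lies in what was put in as the effect, and the criticism should be read that way.
- **The 0.6 is called a minimum, so setting every predictor there is the least favourable corner.** Part of this stands. The 22% and 48% are not fixed values, and if all eight correlations were 0.70, then 132 subjects would be enough. But equal values are not the worst case, as the 15% for one predictor at 0.6 among seven at 0.65 shows. A minimum simple correlation cannot ensure a minimum power for each coefficient.
- **Read as a partial correlation, 0.6 gives ample power.** It does, above 99% even at 45. But the article describes 0.6 as the correlation between predictors and outcome, a VIF would not then be needed, and the implied R² is 0.97.
- **The weight is limited.** This stands. The regression is an additional baseline analysis, 53 did not set the trial size, and the randomised comparison is untouched. At 132 the expected number of significant coefficients is 8 × 0.476 = 3.8, so about half rather than nearly all would be missed. Whether readers would misinterpret those is a risk, not a certainty.
- **A loss allowance is not unreasonable at baseline,** since questionnaires or blood samples can be missing. This also stands in part, though follow-up dropout is not the relevant loss, because baseline assessment precedes randomisation.

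**Conclusion.** The concern holds. Under the protocol's stated correlations, with all predictors at 0.6 and a common inter-predictor correlation of 0.5, power per coefficient is about 22% at 53 subjects and 48% at 132, and about 381 analysed subjects are needed for 90%. The claim of 90% power at 53 fails in every row of the sensitivity table, and 132 reaches 90% only if all predictor-outcome correlations are clearly above the stated minimum. Both the power figure and the feasibility conclusion should be corrected. The results rest on a two-sided test, an equal-correlation structure (the one that reproduces 53) and 0.6 being a simple correlation, as the text describes it. The primary analysis and the trial size are not affected.

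**What to change.** Reword the paragraph in Statistics: Additional analyses:

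- Withdraw the figure of 53 and the statement that the main sample size makes these tests feasible.
- State instead what the available sample gives: with 132 participants at baseline, 8 predictors and two-sided alpha 0.05, 90% power for a partial correlation of about 0.27 to 0.28 or larger.
- Drop the 15% loss, or describe it as an allowance for missing baseline data rather than dropout.
- Call the regression exploratory and report each coefficient with its confidence interval, so that a non-significant coefficient is not read as no contribution.

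The cost is one paragraph and a less favourable stated power. Recruitment, design and the primary analysis stay as they are.
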